### Measures of moderating variables

Data will be gathered regarding demographic variables, child’s developmental age, working alliance between parent and VIPP-V intervention worker and empathy of the VIPP-V intervention worker to determine whether there are certain subgroups for whom or circumstances under which VIPP-V is most effective.

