#### Working alliance between parent and VIPP-V intervention worker

The therapeutic alliance has been found to predict treatment outcomes and seems an important aspect of successful intervention [36]. Therefore, the Dutch translation of the short version of the **Working Alliance Inventory (WAI)** [37–40] will be administered to both the parent and the VIPP-V intervention worker at post-test to assess their feelings of working alliance. This questionnaire consists of 12 items, measuring general alliance as well as three specific aspects of alliance (Bond, Goals and Tasks). An examples of an item is: *“We* (the parent and VIPP-V intervention worker) *have established a good understanding of the kind of changes that would be good for me and my child.”* Items are scores on a 5-point scale, ranging from *“never (1)”* to *“always (5).”* Validity and reliability of the original English version has been demonstrated to be good [37]. During VIPP-V the VIPP-V intervention worker also fills out a notebook and profile of the participating parent after every home-visit to report on the course of the visit, the collaboration with the parent and the progress the parent has made between visits. This notebook and profile will be used to support the data gathered on the WAI.

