### Sample size calculation

The total sample size is based on an expected effect size of *d* = 0.33 (*f* = 0.17), based on a meta-analysis on RCTs of interventions focusing on improving maternal sensitivity [15]. Based on an alpha of 0.05 and a sample of 100 families, adequate statistical power will be achieved (0.97) for testing the significance of an interaction effect between the between-subject factor (experimental versus control condition) and the within-subject factor (assessment: pretest, post-test, follow-up) in repeated measures analysis of variance (ANOVA) using the full sample of 100 families. If, due to circumstances such as drop-out, illness of VIPP-V intervention workers or unexpected organizational aspects, the number of families drops, with an effect size this high, high power (0.80) can still be achieved with 58 families for the main research question regarding effectiveness of intervention on parental sensitivity. However, to also perform moderator analyses with adequate power we aim to include 100 families in the study.

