### Data analysis

All analyses will be done using the software program SPSS (version 21.0). Baseline characteristics will be described in descriptive analyses. Before analyzing, differences in baseline characteristics between the experimental and control condition will be checked. If differences are found, they will be reported and controlled for in further analyses. Before analyzing, outliers will be checked and winsorized if necessary. For analyses of the primary and secondary outcome measures of the study (parental sensitivity, parent-child interaction quality, parental self-efficacy and parenting stress) ANOVA repeated measures or multilevel analyses will be used, depending on the level of clustering in the data. Intention-to-treat and completer analyses will be performed. The primary and secondary outcome measures of families in the experimental condition will be compared with their own scores on a previous assessment, as well as with scores of families in the control condition at the same assessment. Change over time from pretest to post-test and from pretest to follow-up in parental sensitivity, quality of parent-child interaction, parental self-efficacy and parenting stress will be assessed in the experimental group, and compared with the control group. Results will be described as rates of change. The outcome measure regarding feasibility of the intervention ‘Experiences of VIPP-V intervention workers with VIPP-V during early intervention’ will be reported in descriptive analyses. Multivariate regression analysis or multilevel moderator analyses will be performed with different predictors (demographic variables, child’s developmental age, working alliance between parent and VIPP-V intervention worker, empathy of the VIPP-V intervention worker) to study for whom and under which circumstances VIPP-V intervention is most effective. For these analyses only the data of the families in the VIPP-V intervention condition will be used.

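### Moderator analyses confined to the VIPP-V arm cannot show whether demographics or developmental age change the effect of VIPP-V, and the adequate power claimed for them is not supported

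*Protocol article*

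**What the plan says.** Measures of moderating variables gives the purpose of collecting demographics, developmental age, working alliance and worker empathy: "to determine whether there are certain subgroups for whom or circumstances under which VIPP-V is most effective". Data analysis repeats that purpose, offers multivariate regression or multilevel moderator models, and fixes the data set: "For these analyses only the data of the families in the VIPP-V intervention condition will be used". With 1:1 allocation of 100 dyads (Abstract, Study design), that is 50 families at most.

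The Sample size calculation section says that 58 families give power 0.80 for the main question. It then explains the larger target: "However, to also perform moderator analyses with adequate power we aim to include 100 families in the study". It gives no effect size and no power figure for a moderator. Its value of 0.97 belongs to a different test, the interaction of condition with the "within-subject factor (assessment: pretest, post-test, follow-up) in repeated measures analysis of variance (ANOVA) using the full sample of 100 families".

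On where the moderator data exist:
- **Demographics** are obtained before families are enrolled in a block and randomized (Procedure), so both arms have them.
- **Developmental age** comes from the VABS, completed around pretest by the worker who gives care-as-usual (Child's developmental age). Both arms receive care-as-usual.
- **Working alliance** "will be administered to both the parent and the VIPP-V intervention worker at post-test". Control families are not asked about it (Blinding).
- **Empathy** is a trait of the VIPP-V worker and has no counterpart in the control arm.

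**The concern.** The Trial objective, Hypotheses and Primary outcome measures sections all define effectiveness as improvement beyond care-as-usual alone. A moderator of effectiveness is then a variable across which the difference between arms varies. Among treated families only, the slope of change on a covariate is the sum of two parts: the slope that would have been seen without VIPP-V, and the extra slope due to VIPP-V. One arm cannot separate them.

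The children are aged 1 to 5 and are followed for about eight months, so age or developmental level could plausibly relate to change in either arm. A variable that does so equally in both arms would be reported as marking the families for whom VIPP-V works best. Identifying predictors of effectiveness is part of the trial objective and stands beside the aim of preparing wider implementation, so the label matters.

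The second issue is power. The step from 58 to 100 families is justified by power for moderators, but that power is not stated, and the only power figures given are for another test.

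**Working it through.** **1. The protocol's own figures.** Inputs from Sample size calculation: f = 0.17, alpha 0.05, 2 groups, 3 assessments. The correlation between assessments is not stated; 0.5 is assumed. For the within-between interaction, lambda = N·f²·m/(1 − rho), with df (m − 1) and (N − 2)(m − 1).
- N = 100: lambda = 100 × 0.0289 × 3/0.5 = 17.34, df 2 and 196, power 0.967.
- N = 58: lambda = 10.06, df 2 and 112, power 0.807.

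Both stated values (0.97 and 0.80) reproduce. With rho from 0.3 to 0.7, power at N = 100 runs from 0.89 to 0.999. None of this bears on a one-arm regression on a covariate.

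**2. Power of the one-arm analysis.** By Fisher z, the correlation detectable with 80% power (two-sided 0.05) is r = tanh[(1.960 + 0.842)/√(n − 3)].
- n = 50: tanh(2.802/6.856) = tanh(0.409) = 0.387.
- n = 100, for comparison: tanh(2.802/9.849) = tanh(0.284) = 0.277.

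A noncentral F calculation for one regression coefficient gives 0.375 and 0.272. At r = 0.3, power is Φ(0.3095 × √47 − 1.960) = 0.56 with 50 families and 0.86 with 100.

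**3. What the larger target buys.** Under 1:1 allocation, 58 families give a VIPP-V arm of 29 and 100 families give 50. By the noncentral F calculation, the detectable r falls from about 0.48 to 0.375.

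**4. Prognosis read as moderation.** Assumptions: 50 families per arm, a treatment effect of 0.33 SD, and a covariate correlated r with change in both arms, with no interaction. The values of r are illustrative; the protocol gives none. Simulated rejection rates, 4,000 runs per setting:

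| r in both arms | One-arm test | Condition-by-moderator test |
|---|---|---|
| 0.2 | 29% | 5% |
| 0.3 | 58% | 5% |
| 0.4 | 83% | 6% |

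A repeat with 10,000 runs gave 29%, 57% and 83%, against 5% in every row.

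**5. Power of the interaction test in all 100 families.** For a moderator scaled to SD 1, the variance of the slope difference is v × (1/50 + 1/50) = 4v/100, where v is the residual variance (assumed). The detectable difference at 80% power is 2.802 × √(4v/100):
- v = 1: 0.56
- v = 0.75: 0.49
- v = 0.5: 0.40

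These are in SD of the outcome per SD of the moderator. For a binary moderator with four cells of 25 and v = 1, power is 0.24 for a subgroup difference in effect of 0.5 SD and 0.52 for 0.8 SD. A one-arm comparison of 25 with 25 families has power 0.81 for a difference of 0.8 SD, but it answers a different question.

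**The case against.** **The two sections do not contradict each other.** A reader might infer that the sample-size rationale collapses because 100 families are justified by analyses that use 50. The text does not support that. Sample size calculation never says that the moderator analyses use all 100 families, and the larger target does raise the VIPP-V arm from about 29 to 50. What remains is that adequate power is asserted without a figure.

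**For two of the four predictor groups the restriction is unavoidable.** Alliance and VIPP-V worker empathy do not exist in the control arm. This stands, and for these only the description is at issue. It would also be tempting to fault the plan for ignoring that families share 23 workers, but multilevel moderator analysis is already offered. Nor would relating post-test alliance to follow-up instead of post-test outcomes settle the direction of effect, because change from T1 to T3 contains the change from T1 to T2.

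**The simulated percentages rest on assumed correlations.** This is correct. They are the power to detect a real prognostic association. They show how readily one would be misread if it existed, and are not an error rate of this trial.

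**Little depends on these analyses.** Neither main hypothesis involves a moderator, and no section says that implementation will be targeted by moderator results. This stands too, and it limits the weight of the point.

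**VABS data in controls are inferred.** No sentence says outright that the VABS is completed for control families, and the schedule figure is not shown. The inference is strong: the rater is the care-as-usual worker, both arms have care-as-usual, and working alliance is the only questionnaire difference between arms that Blinding names.

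**Conclusion.** The point holds for a secondary analysis. For demographic variables and developmental age, the stated one-arm analysis yields predictors of change among treated families and not evidence of for whom VIPP-V adds benefit. Under the assumed correlations of 0.2 to 0.4 in both arms with no moderation, it would be significant in about 29% to 83% of trials, against about 5% for the interaction test. The claim of adequate moderator power is unsupported: about 50 families give 80% power only for r of about 0.38 to 0.39, before any loss from drop-out or clustering.

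Using both arms corrects the question but does not deliver adequate power. With 100 families, only slope differences of about 0.40 to 0.56 SD per SD of moderator (residual variance 0.5 to 1, assumed) reach 80%. The comparison between arms on the primary and secondary outcomes is untouched.

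**What to change.** 1. In Data analysis, test demographic variables and VABS developmental age as condition-by-moderator interactions in the outcome model, using all randomized families, and label these tests exploratory. Confirm that the VABS is completed for control families.
2. Keep the one-arm analysis for working alliance and worker empathy, but describe both as predictors of outcome among treated families and not as moderators, here and in Measures of moderating variables.
3. In Sample size calculation, replace the statement on moderator power with figures: 80% power for r of about 0.38 to 0.39 in one-arm analyses of about 50 families, and for slope differences of about 0.40 to 0.56 SD per SD of moderator in interaction tests with 100 families, with the residual variance assumed. The reason for preferring 100 to 58 can stay if it is put as raising the VIPP-V arm from about 29 to 50.

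The cost is wording and analysis work, with no new data collection provided that the VABS is held for both arms. The drawback is that interaction tests have low power and are less likely to reach significance, so a null result must not be read as showing that VIPP-V works equally well for all families.

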### Data management and monitoring

All data will be collected through computerized assessments, which obviates the need for double data entry. A Data Monitoring Committee has not been established, because of minimal risks for involved participants. The funding organization of this study (ZonMw InZicht) will conduct a site visit halfway through the project to check on its progress. This study is embedded in the EMGO+ Institute for Health and Care Research of the VU University Medical Center in Amsterdam, The Netherlands. The quality committee of EMGO+ has created an electronic quality assurance handbook to uniform the conduct and safeguard the quality of research within the institute. In addition, EMGO+ does random project audits to assure the quality of all projects. This study adheres to the quality handbook and anticipates the possibility of being randomly audited.

### Protection of data privacy

After informed consent for participation in the study is obtained, all participating families will be assigned a number. Key lists of number – personal data combinations will be stored separately from the data and will be deleted when all data analyses are completed. Data will be analyzed in a way that no conclusions can be drawn about individual participants. All data will be stored on a password-protected server, and if applicable, in lockable cabinets in lockable rooms. All (assistant) researchers with access to the data will sign a non-disclosure statement, which states they will not disclose any information about research participants to a third party.

### Publication policy

Results of this study will be published in peer-reviewed, international journals. To bring the study results to the attention of practitioners who need to implement them, we also plan to publish at least one paper in a national journal within the field of visual disabilities/intellectual disabilities studies. Results will be presented at international scientific conferences and national conferences within the field of disability research. All authors will have access to the full dataset and will have equal opportunity to publish on the dataset. The use of professional writers is not planned.

### Ethical considerations

The Medical Ethics Committee of the VU University Medical Center in Amsterdam, The Netherlands has approved the study protocol (METc VUmc 2013/449/NL47334.029.13). Possible future changes to the study procedures will be proposed to the Medical Ethics Committee as amendments, and will be described and discussed in the publication of the study results hereinafter.

## Discussion

As the need for support in families with a child with a visual disability is clear [1–3], these families should receive the best possible support. Although several early intervention services have been developed that offer support in adapting to the disability and promoting optimal development, these interventions are not yet evidence-based and not transferable through written protocols. This study aims to provide insight into the effectiveness of an adaptation of Video-feedback Intervention to promote Positive Parenting (VIPP) for this specific population (VIPP-V) and to fill a gap in the knowledge about evidence-based treatment for families with a young child with a visual or visual-and-intellectual disability.

VIPP-V is a short intervention, with only seven home-visits over a period of five months. This intervention can be implemented on top of care-as-usual. Short-term interaction-based interventions (fewer than 16 sessions) have been shown to be effective in increasing parental sensitivity and children’s attachment security [15]. A short-term intervention limits the intervention burden for participating families.

Before implementation of this new intervention, a small survey was carried out among 16 parents with a child aged 4–5 years, who already received care from Royal Dutch Visio or Bartiméus. In this survey VIPP-V was described and presented as an intervention which may be offered in the future. Parents were asked how useful they rated this intervention and how likely they would participate. Ratings showed VIPP-V as highly useful (a mean score of 8 out of 10) and parents responded they would likely participate in the intervention if it would be offered (a mean score of 6 out of 10). This small survey supports the relevance of efforts to develop interventions aimed at improving parent-child interaction in families with a child with a visual or visual-and-intellectual disability. Next, a pilot-study of this new intervention was conducted among parents (*N* = 10) and VIPP-V intervention workers (*N* = 8). Participating parents and VIPP-V intervention workers reported positive results after participating in VIPP-V; both parents and intervention workers rated the individual approach with video-feedback and the provision of information on the visual disability as (very) effective (a mean score of 4 out of 5). In addition, parents and VIPP-V intervention workers indicated that the attitude of the parent towards the child, as well as the parent-child interaction was improved. Also, both parents and VIPP-V intervention workers reported an increase in parental self-efficacy. These descriptive findings of both the survey and the pilot suggest benefits from VIPP-V, compatibility with existing services for parents of children with a visual or visual-and-intellectual disability and provide a basis for further research on the effectiveness of this video-feedback intervention.

A strength of the study is the close collaboration with two national organizations, both with multiple rehabilitation centers throughout The Netherlands. In case our results show the effectiveness of VIPP-V, this new intervention can be immediately continued as a component of already offered services for parents of a child with a visual or visual-and-intellectual disability. National centers providing support for parents of children with a visual disability have the responsibility to provide evidence-based interventions during early intervention. Close collaboration between practice and science is, therefore, key to respond to the wishes of parents for more information and help in improving parent-child interaction quality.

In conclusion, this study will provide insight into the effectiveness of an attachment-based video-feedback intervention for parents of children with a visual or visual-and-intellectual disability and, if the intervention is effective, prepare the field for broad-scale implementation.

## Status of the trial

The study started in September 2013. After being granted permission by the Medical Ethics Committee to start with the inclusion of research participants, the first families were included in February 2014. Currently, data collection is in progress. The main results are expected to be published in the beginning of 2016.

## Abbreviations

ANOVA: Analysis of variance
EQ-short: Empathy Quotient questionnaire short-version
ICC: Intraclass Correlation Coefficient
METc: Medical Ethics Committee
NICHD scales: National Institute of Child Health and Human Development Scales
PSI: Parental Stress Index
RCT: Randomized Controlled Trial
SENR: Self-efficacy in the Nurturing Role questionnaire
T1: First assessment
T2: Second assessment
T3: Third assessment
USB: Universal Serial Bus
VABS: Vineland Adaptive Behavior Scales
VIPP: Video-feedback Intervention to promote Positive Parenting
VIPP-AUTI: Video-feedback Intervention to promote Positive Parenting adapted to Autism
VIPP-LD: Video-feedback Intervention to promote Positive Parenting and sensitive disciplining for parents with Learning Difficulties
VIPP-SD: Video-feedback Intervention to promote Positive Parenting and Sensitive Discipline
VIPP-V: Video-feedback Intervention to promote Positive Parenting in parents of children with Visual or visual-and-intellectual disabilities
VUmc: VU University Medical Center
WAI: Working Alliance Inventory
WHO: World Health Organization
